#### Sleep-related assessments

2.4.1

The sleep assessment battery was designed to capture multiple dimensions of sleep health and related behaviors that contribute to the pathophysiology of insomnia.

*Primary sleep measures*: The Insomnia Severity Index (ISI) (21, 22) serves as the primary outcome measure for insomnia severity, administered at screening for group allocation (≥15 for the insomnia group; <8 for controls) and weekly thereafter via the SOMDAY application. The Pittsburgh Sleep Quality Index (PSQI) (23, 24) assesses global sleep quality over the past month, whereas the Sleep Health Index (SHI) (25) provides a comprehensive measure of sleep health across multiple domains.

*Sleep disorder screening*: The Epworth Sleepiness Scale (ESS) (26, 27) measures daytime sleepiness, the Berlin Questionnaire (BQ) (28, 29) screens for obstructive sleep apnea risk, and the International Restless Legs Syndrome Rating Scale (IRLS) (30) assesses RLS (Restless Legs Syndrome) symptom severity.

*Sleep-related behaviors and cognitions*: Several instruments assess factors known to perpetuate insomnia. The Sleep Hygiene and Practices Scale (SHPS) (31, 32) evaluates sleep hygiene behaviors, whereas the Dysfunctional Beliefs and Attitudes about Sleep-16 (DBAS-16) (33) measures maladaptive sleep-related cognitions. The Morningness-Eveningness Questionnaire (MEQ) (34, 35) determines chronotype, Bedtime Procrastination Scale (BPS) (36) assesses bedtime delay behaviors, and Ford Insomnia Response to Stress Test (FIRST) (37) measures vulnerability to stress-induced sleep disturbance.

##### Insomnia Severity Index

2.4.1.1

The ISI is a seven-item self-reported scale rated from 0 to 4 per item, with a total score ranging from 0 to 28. This scale assesses difficulty in initiating and maintaining sleep, early morning awakening, satisfaction with sleep, daytime functional impairment, impact on quality of life as observed by others, and worry about sleep problems. Scores of 0–7 indicate no clinically significant insomnia, 8–14 indicate mild insomnia, 15–21 indicate moderate clinical insomnia, and 22–28 indicate severe clinical insomnia. The ISI demonstrates a Cronbach’s α of 0.83, which reflects good internal consistency across diverse populations (38). In this study, the ISI is administered at screening to allocate participants (ISI ≥ 15 for the insomnia group; ISI < 8 for the control group), and thereafter, it was administered weekly to evaluate the subjective insomnia severity.

##### Pittsburgh Sleep Quality Index

2.4.1.2

The PSQI is a 19-item self-report questionnaire that evaluates sleep quality across seven domains: subjective quality, latency, duration, efficiency, disturbances, medication use, and daytime dysfunction over the past month, yielding a global score ranging from 0 to 21. Each domain is scored from 0 to 3, with higher scores reflecting poorer sleep, and a global PSQI score >5 reliably distinguishes poor sleepers from good sleepers.

##### Sleep Health Index

2.4.1.3

The SHI, developed by the National Sleep Foundation, is a validated self-report instrument designed to assess general sleep health in adults. It comprises 14 items grouped into three subdomains: sleep quality, sleep duration, and disordered sleep. Each subdomain contributes to a composite score ranging from 0 to 100, with higher scores indicating better sleep health.

##### Epworth Sleepiness Scale

2.4.1.4

The ESS is a self-administered scale designed to measure average daytime sleepiness. This scale consists of eight items representing specific situations describing hypothetical situations such as sitting and reading, watching television, sitting inactive in a public space, riding as a passenger in a car for an hour without a break, lying down to rest in the afternoon, sitting and talking to someone, sitting quietly after a lunch without alcohol, and sitting in a car while stopped for a few minutes in traffic. Each item is rated on a 0–3 scale (0 = none, 1 = slight, 2 = moderate, 3 = high), resulting in a total score ranging from to 0-24.

##### Berlin Questionnaire

2.4.1.5

The BQ is a 10-item self-report tool supplemented by height and weight data designed to assess obstructive sleep apnea (OSA) risk across three categories: snoring, witnessed apneas, daytime sleepiness and fatigue, and obesity/hypertension. A respondent is classified as high risk for OSA if two or more domains met the predefined positivity criteria. Categories 1 and 2 are considered positive if the total score is ≥2. Category 3 is considered positive if the participant has hypertension or BMI ≥25 kg/m^2^.

##### Restless Legs Syndrome Rating Scale

2.4.1.6

The IRLS is a 10-item self-reported scale assessing core RLS symptoms, intensity and frequency, sleep disturbance, and impact on mood and daytime functioning. The total score ranges from 0 to 40, with higher scores indicating greater severity. Severity is classified as mild (0–10), moderate (11–20), severe (21–30), or very severe (31–40).

##### Sleep Hygiene and Practices Scale

2.4.1.7

The SHPS is a 30-item self-report scale that captures a wide range of behaviors and environmental factors that may interfere with sleep. It is organized into four domains: arousal-related behaviors, sleep scheduling and timing, eating and drinking behaviors, and sleep environment. Each item is rated on a six-point Likert scale from 1 (never) to 6 (always), yielding a total score between 30 and 180, where higher scores indicate poorer sleep hygiene.

##### Dysfunctional Beliefs and Attitudes about Sleep-16

2.4.1.8

The DBAS-16 assesses maladaptive sleep-related cognition using 16 items rated from 0 to 10 (“strongly disagree” to “strongly agree”). It evaluates four key domains: perceived consequences of insomnia, worry and helplessness about sleep, unrealistic sleep expectations, and beliefs regarding sleep medication. A global score is computed as the mean of all items (range 0–10), with higher total scores reflecting more dysfunctional sleep-related beliefs and greater cognitive contribution to sleep difficulties.

##### Morningness-Eveningness Questionnaire

2.4.1.9

The MEQ is a 19-item self-report instrument uses to determine an individual’s chronotype based on preferred times for sleep/wake times, preferred times for activities, and subjective alertness. Items include a mixture of Likert-type and time-scale questions, each scored from 1 to 5, yielding a global score ranging from 16 to 86, with higher scores reflecting stronger morning preferences and lower scores reflecting stronger evening preferences.

###### Bedtime Procrastination Scale

2.4.1.10

The BPS is a 9-item self-report measure designed to assess the tendency to delay bedtime without external justification, capturing a broad range of behaviors leading to insufficient sleep. Each item is rated on a five-point Likert scale from 1 (almost never) to 5 (almost always), resulting in total scores between 9 and 45, with higher scores indicating greater bedtime procrastination.

###### Ford Insomnia Response to Stress Test

2.4.1.11

The FIRST is a 9-item self-report tool that assesses sleep reactivity, that is, the propensity to experience sleep disturbances in response to common stressful scenarios. Items describe situations such as work deadlines, social conflicts, or caffeine consumption, each rated on a four-point scale from 1 (not likely) to 4 (very likely), yielding a total score between 9 and 36, with higher scores indicating greater vulnerability to stress-induced insomnia.

#### Psychological and mental health assessments

2.4.2

Given the strong bidirectional relationship between sleep and mental health, comprehensive psychological assessment is essential for phenotyping.

Current symptom severity is assessed using the Generalized Anxiety Disorder-7 (GAD-7) (39) and Patient Health Questionnaire-9 (PHQ-9) (40), both to be administered at the baseline and endpoint. The State-Trait Anxiety Inventory (STAI) (41) measures situational and dispositional anxiety. The Body Sensations Questionnaire (BSQ) (42) assesses anxiety sensitivity, particularly fear of autonomic sensations. The Korean version of the Mood Disorder Questionnaire (K-MDQ) (43, 44) screens for bipolar spectrum disorders using a simplified scoring algorithm (≥7 positive responses). The Korean Resilience Quotient-53 (KRQ-53) (45, 46) measures psychological resilience across emotion regulation, optimism, and problem-solving domains.

##### State-Trait Anxiety Inventory

2.4.2.1

The STAI is a 40-item self-report inventory that measures two types of anxiety: state anxiety (how one feels “right now”) and trait anxiety (how one generally feels). Each subscale contains 20 items rated on a 4-point Likert scale from 1 (“almost never”) to 4 (“almost always”), yielding scores from 20 to 80 per subscale, with higher scores indicating greater anxiety levels.

##### Generalized Anxiety Disorder-7

2.4.2.2

The GAD-7 is a brief, 7-item self-report scale designed to screen for generalized anxiety disorder and assess its severity over the prior two weeks. Each item is rated on a 4-point scale, ranging from 0 (“not at all”) to 3 (“nearly every day”), resulting in a total score of 0–21. The severity cutoffs are 5 (mild), 10 (moderate), and 15 (severe), with scores ≥ 10 warranting further evaluation.

##### Patient Health Questionnaire-9

2.4.2.3

The PHQ-9 is a 9-item self-administered measure of depressive symptoms based directly on the DSM-IV criteria, covering the frequency of symptoms over the past two weeks. Items are scored from 0 (“not at all”) to 3 (“nearly every day”), yielding a total score of 0–27. Standard severity thresholds are 5–9 (mild), 10–14 (moderate), 15–19 (moderately severe), and 20–27 (severe).

##### Body Sensations Questionnaire

2.4.2.4

The BSQ is a 17-item self-report inventory that assesses the degree of fear elicited by the common autonomic sensations associated with anxiety. Each item (e.g., heart palpitations, dizziness, shortness of breath) is rated on a 5-point Likert scale, ranging from 1 (“not frightened or worried”) to 5 (“extremely frightened or worried”), with higher averages reflecting greater tendencies toward catastrophic misinterpretation.

##### Korean version of Mood Disorder Questionnaire

2.4.2.5

The Mood Disorder Questionnaire (MDQ) is a 13-item self-report screening tool for lifetime manic or hypomanic symptoms, indicative of bipolar spectrum disorders. It comprises three sections: (i) 13 yes/no items assessing lifetime manic/hypomanic symptoms; (ii) a question asking whether two or more endorsed symptoms occurred during the same period; and (iii) an item rating functional impairment on a scale from none to severe. In this study, we will use the validated Korean version of the Mood Disorder Questionnaire (K-MDQ), which applies a simplified scoring algorithm that considers only the section 1 symptom count. A cutoff of ≥7 yes responses indicates a positive screen, irrespective of symptom co-occurrence or impairment ratings.

##### Korean Resilience Quotient-53

2.4.2.6

The KRQ-53 is a 53-item self-report instrument that measures psychological resilience across three core domains, emotion regulation, optimism, and problem-solving capacity, each represented by 17–18 items. Items use a 5-point Likert scale ranging from 1 (“strongly disagree”) to 5 (“strongly agree”), generating total and subscale scores that reflect one’s ability to adapt to stress and adversity.

#### General health and lifestyle assessments

2.4.3

Additional instruments capture broader health and lifestyle factors that influence sleep and can confound study outcomes.

*Physical health and functioning*: The Multidimensional Fatigue Scale (MFS) (47) assesses fatigue across the general, sleep/rest, and cognitive domains. The WHO Quality of Life-BREF (WHOQOL-BREF) (48) measures perceived quality of life across four domains: physical, psychological, social, and environmental.

*Substance use and lifestyle factors*: The Alcohol Use Disorders Identification Test (AUDIT) (49, 50) screens for problematic alcohol use. The International Physical Activity Questionnaire-Short Form (IPAQ-SF) (51, 52) quantifies physical activity levels across walking, moderate, and vigorous-intensity activities.

*Circadian and seasonal factors*: The Biological Rhythms Interview of Assessment in Neuropsychiatry (BRIAN) (53, 54) assesses disturbances in circadian rhythms across sleep, social, activity, and eating domains. The Seasonal Pattern Assessment Questionnaire (SPAQ) (55) screens to assess seasonal mood variations.

*Technology use and spiritual well-being*: The Smartphone Overuse Screening Questionnaire (SOS-Q) (56) assesses smartphone addiction risk, whereas the Spiritual Well-Being Scale (SWBS) (57) measures religious and existential well-being.

##### Multidimensional Fatigue Scale

2.4.3.1

The Multidimensional Fatigue Scale is an 18-item self-report questionnaire that evaluates three domains of fatigue—general fatigue, sleep/rest fatigue, and cognitive fatigue—using six items per domain. Each item is rated on a five-point Likert scale from 1 (“never”) to 5 (“almost always”), yielding subscale scores of 6–30 and a total score of 18–90, with higher scores indicating greater fatigue.

##### Alcohol Use Disorders Identification Test

2.4.3.2

The Alcohol Use Disorders Identification Test (AUDIT) is a 10-item screening instrument that assesses alcohol consumption, dependence, and alcohol-related problems. Most items are rated 0–4; two items use a 0, 2, and 4 scoring format, with a total score between 0 and 40. A score of 8 or above suggests hazardous drinking that warrants further assessment, whereas higher cutoffs (e.g., ≥ 20) indicate probable alcohol dependence. This study will also use the Alcohol Use Disorders Identification Test-Consumption (AUDIT-C), a three-item consumption subscale of the AUDIT, to screen for hazardous drinking and possible alcohol use disorder. Each AUDIT-C item is scored 0–4, yielding a total score of 0–12. Sex-specific cut-offs are applied as follows: ≥4 for men and ≥3 for women.

##### Smartphone Overuse Screening Questionnaire

2.4.3.3

The SOS-Q is a 28-item self-report screening questionnaire, with each item rated on a 4-point scale that identifies smartphone use habits and screens for smartphone addiction risk. The cutoff score is 49, and scores higher than 49 indicate a high risk of smartphone addiction.

##### International Physical Activity Questionnaire–Short Form

2.4.3.4

The IPAQ-SF is a 7-item self-report measure of physical activity and sedentary behavior over the previous seven days. Participants report the number of days and average minutes per day they spent walking, performing moderate-intensity activities, and vigorous-intensity activities, as well as total sitting time. Responses are converted into metabolic equivalents-minutes per week to quantify the total activity volume.

##### WHO Quality of Life–BREF

2.4.3.5

The WHOQOL-BREF is a 26-item self-report instrument derived from the WHOQOL-100 that assesses perceived quality of life across four domains: Physical Health, Psychological Health, Social Relationships, and Environment. Each item is rated on a five-point Likert scale, and raw domain scores are transformed to a 0–100 scale, where higher scores denote better quality of life. It includes two global items on overall quality of life and general health perception.

##### Seasonal Pattern Assessment Questionnaire

2.4.3.6

The SPAQ is an 8-item self-report screener for seasonal affective changes in six behavioral and mood dimensions: sleep length, social activity, mood, weight, appetite, and energy. Each dimension is rated from 0 (“no change”) to 4 (“extremely marked change”), yielding a Global Seasonality Score (GSS) of 0–24. An additional severity item asks respondents to rate the degree of problems experienced due to these seasonal changes. A GSS ≥ 11 combined with moderate or marked problem severity indicates probable seasonal affective disorder.

##### Biological Rhythms Interview of Assessment in Neuropsychiatry

2.4.3.7

BRIAN is an 18-item instrument designed to quantify circadian rhythm disturbances. It covers four primary domains (sleep patterns, social rhythms, activity levels, and eating behaviors) and includes three additional items for classifying an individual’s predominant rhythm (chronotype). Each item asks how often respondents experience disruption in maintaining a regular biological rhythm, rated on a four-point scale from 1 (“not at all”) to 4 (“very much”), resulting in a total score of 18–72, with higher scores indicating more severe circadian dysregulation.

##### Spiritual Well-Being Scale

2.4.3.8

The Spiritual Well-Being Scale is a 20-item self-report measure of perceived spiritual quality of life, divided into two 10-item subscales: Religious Well-Being (RWB) and Existential Well-Being (EWB). Items are rated on a six-point Likert scale from 1 (“strongly disagree”) to 6 (“strongly agree”), yielding subscale scores of 10–60 and a total score of 20–120, with higher scores indicating greater spiritual well-being.

#### Assessment schedule and administration

2.4.4

Clinical assessments are strategically scheduled to minimize the participant burden while capturing baseline characteristics and changes over the study period. Baseline assessments encompass a comprehensive battery of evaluations to establish a complete phenotype. Weekly assessments via the SOMDAY application focus on dynamic measures (e.g., ISI) to monitor symptom trajectories. Endpoint assessments (week 4) repeat the key measures (ESS, PHQ-9, GAD-7, MFS, IPAQ-SF, and WHOQOL-BREF) to evaluate changes in mental health, fatigue, physical activity, and quality of life.

### Digital phenotyping

2.5

Digital phenotyping serves as a core methodological component of this study, using a wearable device and smartphone application for continuous monitoring of participants’ behavioral and physiological parameters. A custom-designed smartphone application, named “SOMDAY” (Lumanlab Inc., Seoul, Republic of Korea), is installed on the participants’ personal smartphones. The name combines “SOM” (from ‘somnus,’ the Latin word for sleep) and “DAY,” reflecting the key principle of circadian rhythms that optimizing daytime activities is crucial for improving nighttime sleep. The application is compatible with both the Android OS and iOS platforms.

Participants are provided with a wrist-worn wearable device (Fitbit Inspire 3, Fitbit Inc., USA) and are instructed to wear it throughout the 4-week study period, except for charging or if it causes significant discomfort. This integrated platform, consisting of a Fitbit device and a SOMDAY application, enables both passive and active data collection. The digital data to be collected for this study is categorized into four main domains: (1) sleep metrics, (2) activity data, (3) heart rate data, and (4) application-derived data.

The first three domains of data, which include sleep metrics, activity data, and heart rate data, are obtained passively from wearable devices and constitute the passive digital phenotyping component. The fourth domain, application data, is collected using a smartphone application and will represent the active digital phenotyping component. These data are processed to derive a comprehensive set of digital phenotypes for subsequent analyses.

#### Passive digital phenotyping data collection

2.5.1

Fitbit devices continuously and passively collect objective data. Sleep metrics, including total sleep time, total awake time, sleep onset latency, sleep efficiency, and duration of sleep stage (light, deep, and REM sleep), are generated daily. Sleep stages are estimated using the Fitbit algorithm, based on a combination of movement and heart rate variability (HRV) patterns. Inactivity for approximately one hour is assumed to indicate sleep, while significant movements is interpreted as wakefulness. Total sleep time is calculated by subtracting the total awake time from the total inactive time.

The devices also collect physiological data, including continuous heart rate data (sampled at 5-minute intervals) and activity data, such as step counts and walking distance. Raw heart rate data will be utilized for cosinor analysis to derive circadian rhythm parameters. Step counts and walking distance, which are recorded as cumulative values, will be used to characterize circadian activity patterns. The data is automatically and wirelessly transmitted from the wearable device to the smartphone application and securely uploaded to a cloud-based research server.

#### Active digital phenotyping data collection

2.5.2

The SOMDAY application will be used to actively collect self-reported data through a series of ecological momentary assessments (EMAs). To capture daily habits and experiences in a timely manner, participants will be prompted to log their daily entries every night at 9 PM. A daily sleep diary collects subjective information, including self-reported sleep duration, perceived sleep quality, and the number of awakenings. Additionally, participants receive daily ratings for their mood and stress levels. Moods are rated on a 7-point scale ranging from -3 (very bad) to +3 (very good), and stress levels are measured on a 4-point scale (0=none, 1=mild, 2=moderate, and 3=severe). The ratings for alcohol and caffeine consumption are collected daily, noting both the amount and the time of intake (morning, afternoon, or night). Detailed information on the time of day is crucial for applying a weighted scoring system during data processing to reflect the differential impact of these substances on the circadian rhythm. Information on smoking is collected as a daily log. Finally, brief questionnaires, such as the ISI, are administered weekly via the application to track longitudinal changes in insomnia severity and other related symptoms throughout the study period.

The SOMDAY application was used to actively collect self-reported data through a series of ecological momentary assessments (EMAs). The daily sleep diary was designed to be completed immediately after awakening, capturing self-reported sleep duration, perceived sleep quality, and the number of nocturnal awakenings. In addition, participants were prompted at 9:00 PM each day to report daily mood and stress levels, as well as alcohol and caffeine consumption.

Mood was rated on a 7-point scale ranging from −3 (very bad) to +3 (very good), and stress levels were rated on a 4-point scale (0 = none, 1 = mild, 2 = moderate, 3 = severe). Daily records of alcohol and caffeine intake included both the amount and the time of consumption (morning, afternoon, or night), allowing for weighted scoring to account for their differential effects on the circadian rhythm. Smoking behavior was also recorded as a daily log. Insomnia Severity Index (ISI) was administered weekly via the application to monitor longitudinal changes in insomnia severity and related symptoms throughout the study period.

#### Data processing and feature generation

2.5.3

The raw digital data from the wearable devices and the SOMDAY smartphone application undergo a rigorous processing pipeline to generate a comprehensive set of digital phenotypes. This approach is not limited to a single analytical plan, and the processed data can be used for various advanced statistical and computational analyses, such as machine learning, to explore the complex relationships between different data modalities and identify meaningful patterns. The processing strategies for each data modality are meticulously designed to provide a rich dataset for subsequent analyses aimed at elucidating biopsychosocial phenotypes of sleep.

The periodic nature of sleep and activity is the key focus of our analysis. Raw data from wearable devices, including continuous heart rate and step counts, will be processed to extract a range of clinically relevant features. For continuous variables such as heart rate and step counts, cosinor analysis (58, 59) will be performed to characterize circadian rhythms. This will involve processing the data within 72-hour intervals to derive key circadian rhythm parameters, including midline estimating statistic of rhythm (MESOR), amplitude, and acrophase. MESOR represents the rhythm-adjusted mean and provides a robust measure of the average parameter level over time. Amplitude quantifies the extent of predictable variation within the circadian cycle, reflecting the strength of the rhythm. The acrophase indicates the timing of the peak value, which offers insight into circadian alignment or misalignment.

In addition, a range of other activity-related metrics will be calculated to provide a more detailed view of daily patterns. These will include the least active 5-hour period (L5), the most active 10-hour period (M10), interdaily stability (IS), and intradaily variability (IV) (60). L5 and M10 will be calculated using the moving average method to identify minimum and maximum activity periods, respectively. IS quantifies the day-to-day regularity of a rhythm, whereas IV measures rhythm fragmentation within a day. These features will be segregated by weekdays and weekends to capture distinct lifestyle patterns.

The raw, continuous heart rate data collected at 5-minute intervals will be a critical component for understanding circadian rhythmicity and autonomic function. We will apply cosinor analysis to these data, similar to the method used for step counts, to extract key rhythm parameters. Specifically, we will derive the MESOR, amplitude, and acrophase of the heart rate rhythm over a 72-hour window. The MESOR of the heart rate rhythm reflects the average heart rate, whereas the amplitude provides a measure of the magnitude of diurnal heart rate fluctuation, which can be an indicator of autonomic nervous system activity. The acrophase of the heart rate rhythm indicates the time of day when the heart rate is at its peak and is a key metric for assessing the phase of the circadian clock. These features will also be calculated separately for weekdays and weekends to account for differences in daily routines and their impact on physiological rhythms. Additionally, heart rate data collected during sleep will be used to derive the resting heart rate (RHR) as a proxy for autonomic nervous system activity, a measure known to be associated with arousal and stress. Heart rate data collected every 5 minutes from the Fitbit Inspire 3 were used to evaluate circadian rhythmicity and autonomic function. Because the device provides pulse rate variability derived from photoplethysmography(PPG) rather than true ECG based HRV, short term beat to beat analyses were not performed. Instead, resting heart rate during sleep and cosinor rhythm parameters were used to indirectly assess long term autonomic patterns. This approach allows for the characterization of autonomic rhythms in real world conditions.

Self-reported data collected via the SOMDAY application will undergo specific processing to reflect the differential impact of behavior on circadian regulation. A time-of-day weighted scoring system will be applied to substances such as alcohol and caffeine, based on their intake time (morning, afternoon, or night). For example, the disruptive potential of caffeine on sleep will be weighted more heavily for intake closer to bedtime. Similarly, stress levels and nap durations will be processed with weights to reflect their influence on circadian rhythms, a key focus of this study.

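### The 72-hour cosinor window cannot be met for separate weekend values; independently, interdaily stability split by weekday and weekend is not on one scale

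*Protocol article*

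**What the plan says.** All the relevant rules stand in section 2.5.3 of the protocol article (Data processing and feature generation).

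- **Cosinor window.** For heart rate and step counts, the cosinor analysis involves "processing the data within 72-hour intervals to derive key circadian rhythm parameters". For heart rate the article says again that "we will derive the MESOR, amplitude, and acrophase of the heart rate rhythm over a 72-hour window".
- **Cosinor split.** A few sentences later, about the heart-rate features: "These features will also be calculated separately for weekdays and weekends to account for differences in daily routines".
- **Activity metrics.** The paragraph on L5, M10, IS and intradaily variability (IV) explains that "IS quantifies the day-to-day regularity of a rhythm, whereas IV measures rhythm fragmentation within a day". It closes with "These features will be segregated by weekdays and weekends to capture distinct lifestyle patterns". It gives no number of days for IS and no adjustment for unequal numbers.

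Section 2.5 says that participants "are instructed to wear it throughout the 4-week study period", with exceptions for charging or discomfort. Section 2.8.1 excludes longer missing periods from time-series analyses. Section 2.8.4 clusters participants on standardized digital phenotyping features.

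**The concern.** There are two separate problems.

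First, the heart-rate cosinor features are defined by a 72-hour window and are then required for weekends alone. An ordinary weekend is shorter than the window, so an analyst has to break one of the two rules, and the text does not say which. If the 72-hour rule is kept, weekday hours enter the weekend values and shrink the weekday–weekend difference that the split is meant to capture. Acrophase matters most here, because the article treats it as a key measure of circadian phase.

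Second, and independently of the 72-hour rule, IS is a ratio whose expected value depends on how many days enter it. There are fewer weekend days than weekdays, so the same degree of regularity gives a higher weekend IS. The same mechanism acts between participants: fewer valid days give a higher IS. Wear time can then pass for regularity in a feature that may be used for subtyping.

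**Working it through.** The article gives no figure of its own on this point, so there is nothing to reproduce first.

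**Inputs.** From the article: a 72-hour window; a 4-week record, which is 28 days with 8 weekend days and 20 weekdays if wear is complete. Assumed: weekend = Saturday and Sunday (48 h); 24 hourly bins for IS; independent noise.

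**1. Overlap of a contiguous 72-hour window with weekdays.**
- The smallest weekday share is (72 − 48)/72 = 24/72 = 33.3%. Enumerating all 168 hourly starting points in a week gives the same minimum of 24 weekday hours.
- Cutting 28 days into nine consecutive 72-hour blocks gives no all-weekend block for any starting weekday. Only 2 or 3 blocks contain both weekend days, and 3 or 4 contain none.

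**2. Effect on acrophase if such a window is used.** Take two weekend days delayed by 2.0 h (30°), one weekday, and equal amplitude. With complete data the fitted phase is the direction of the vector mean:
- angle = arctan[2 sin 30° / (2 cos 30° + 1)] = arctan(1/2.732) = 20.1°, and 20.1/15 = 1.34 h;
- relative amplitude = √(2.732² + 1²)/3 = 2.909/3 = 0.970, a loss of about 3%.

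Delays of 1 h and 3 h are estimated as 0.67 h and 2.02 h. About one third of the shift is lost each time.

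**3. IS and the number of days d.** IS is the between-hour sum of squares of the average day (times d) divided by the total sum of squares.
- *No rhythm:* expected IS = (24 − 1)/(24d − 1).
- *Identical rhythm every day, amplitude = noise SD = 1:* the rhythm has variance 0.5 over the 24 hours. The expected numerator is 24·0.5·d + 23 = 12d + 23, and the expected denominator is 12d + 24d − 1 = 36d − 1. Their ratio approximates the expected IS. The limit for many days is 0.5/1.5 = 0.333.

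| Days | No rhythm | Same rhythm, (12d + 23)/(36d − 1) | Same rhythm, simulated (4000 runs) |
|---|---|---|---|
| 2 (one weekend) | 0.489 | 47/71 = 0.662 | 0.657 |
| 3 | 0.324 | 59/107 = 0.551 | 0.548 |
| 5 (one working week) | 0.193 | 83/179 = 0.464 | 0.461 |
| 8 (weekends pooled) | 0.120 | 119/287 = 0.415 | 0.413 |
| 20 (weekdays pooled) | 0.048 | 263/719 = 0.366 | 0.366 |

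For one and the same rhythm, weekend IS exceeds weekday IS by about 0.20 if computed per week (0.657 − 0.461) and by about 0.05 if pooled over four weeks (0.413 − 0.366).

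**4. Wear.** For the same rhythm, a participant with 4 valid weekend days has an expected IS of about (48 + 23)/(144 − 1) = 71/143 = 0.50, against 0.41 with all 8. The four-day figure is an illustration, since the article reports no wear data. Standardizing the feature across participants removes an offset that all share, but not one that depends on each participant's own day count.

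**The case against.** The article nowhere says that weekend values come from windows containing weekday hours. It says the features are also calculated separately, which can be read as an additional fit on weekend data only, either per 48-hour weekend or pooled over about 8 weekend days. On that reading weekday contamination is zero. How days are extracted and pooled is detail that an article may leave to the full protocol or to code. The cosinor split is explicit only for heart rate. The IS split closes another paragraph and has nothing to do with the 72-hour window. No weekday-minus-weekend contrast is listed in section 2.8; the primary group comparisons are insomnia against control, where an offset common to both groups largely cancels.

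Much of this stands. A reader might infer that every weekend cosinor value is at least one third weekday data. The documents do not support that: it holds only for contiguous 72-hour windows. A reader might also infer that weekends will look more regular whatever the participant does. That is wrong too: pooled, a weekend without rhythm has an expected IS of 0.120, below the 0.366 of a rhythmic working week. The acrophase figures are conditional on the assumptions shown.

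Two things remain. A weekend-only fit escapes contamination only by leaving the 72-hour rule, so the two stated rules still conflict; this is more than omitted detail. The IS problem holds whether IS is computed per week or pooled, and standardization does not remove the part that comes from differing numbers of valid days.

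**Conclusion.** The concern holds in two limited parts.

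- **Cosinor.** The 72-hour window and the separate weekend values cannot both be met with contiguous data, taking the weekend as 48 hours. If contiguous windows are used, at least 33% of each weekend fit is weekday data and about one third of an acrophase shift is lost (2.0 h becomes about 1.34 h, with equal amplitude and one weekday in the window). With weekend-only data there is no such loss.
- **IS.** Weekend and weekday IS are not on the same scale. For an identical rhythm the gap is about 0.20 per week or 0.05 pooled, assuming hourly bins, independent noise with SD equal to the amplitude, and complete wear; other assumptions change the size. Participants with fewer valid days appear more regular. This stems from unequal day counts, not from the 72-hour rule.

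The consequences fall on weekday–weekend contrasts and on clustering features that depend on wear. Insomnia–control comparisons of IS are affected mainly if the number of valid days differs between groups, and the article gives no data on that. Sample size, power, alpha and the ISI outcome are untouched. The change should be made, but it is a matter of feature definition and does not put the study's main conclusions in doubt.

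**What to change.** Amend section 2.5.3 as follows.

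1. Keep 72-hour windows for all-day cosinor features only, and define the weekend.
2. Form weekday and weekend cosinor values from day-type-restricted data: either pool each participant's valid weekend days (and likewise the weekdays) in one fit, or fit one model per participant over all valid days with day-type interactions on MESOR and on the cosine and sine terms.
3. Compute IS on an equal number of valid days per day type and across participants, or correct it for the number of days. One correction replaces the sums of squares by variance components: between-hour variance = (SSB − 23·MSW)/(24d), where SSB is the between-hour sum of squares and MSW the within-hour mean square on 24(d − 1) degrees of freedom. Corrected IS is that variance divided by itself plus MSW. In the example above it targets 0.333 for any number of days.

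The cost is a change to the feature-generation code and about two sentences of text. Data collection is complete and no new data are needed. The downside is that IS on matched days is slightly less precise, and participants below the chosen number of valid days would have no matched value.
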